## Methods

### Objectives

In accordance with the previously discussed background, the present study has four main objectives: the first objective is to determine the efficacy of metformin in combination with a lifestyle intervention in reducing BMI in obese children compared with placebo after 6 months; the second objective is to evaluate the effects on insulin resistance inherent to metabolic syndrome; the third objective is to identify its effects on inflammatory, cardiovascular risk and oxidative stress biomarkers; the fourth objective is to evaluate the change of gut microbiota composition after treatment. Additionally, metformin differential response will be analyzed according to genetic polymorphisms in drug uptake transporter genes.

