### Interventions

The patients are instructed to taking a initial dose of 50 mg twice daily for 10 days, followed by 500 mg twice daily until the end of the treatment. The presentation comprises tablets in opaque, white plastic containers and a side label with 28 units. The dietician centers administer a food frequency questionnaire (FFQ) and a physical activity survey to all participants at the beginning and at the end of the trial. All participants are provided with standardized healthy lifestyle advice at the start of a one-on-one session, including a healthy diet and exercise advice sheet. The participants attend an initial trial baseline visit, followed by three additional visits at 2-month intervals (Fig. 2), which include anthropometric parameter and blood pressure (BP) assessments, as well as a physical examination. A medical history is obtained for each participant, including documentation of the family history.

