### Blood, urine and fecal sampling

General biochemical analyses are performed at the participating hospitals following internationally accepted protocols.

Blood samples are obtained for biochemical and hematological screening tests between 08.30 and 10.30. Three milliliters of blood are collected at the beginning and at the end of the trial. The blood is drawn via the antecubital vein. Peripheral white blood cells (buffy coat) are taken for deoxyribonucleic acid (DNA) extraction. Moreover, a 1-ml urine sample is obtained for oxidation marker analysis. Children should not eat for 12 hours before the sampling. All samples are collected and stored frozen by the research staff. The samples will be analyzed in the clinical laboratory of each hospital, as well as the INYTA.

In order to studying the childrens’ gut microbiota, 100–200 g of fecal sample is collected in a sterile container by parents at the beginning and at the end of the trial. Immediately, all samples are stored frozen until to be analyzed at the INYTA.

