### Sample size

As previously indicated, the principal variable is the BMI *Z* score, on which the sample size calculation was based. Its standard deviation is 2.29 in the least favorable case (according to the tables by Cole et al. [29]), and a desired minimum difference of 2 points is expected. With an *α* error of 0.05, a β error of 0.20 and an estimated follow-up loss of 20 %, four groups in total are planned for the study: two groups of obese children (pre-pubertal and pubertal) treated with metformin and two groups of obese children (pre-pubertal and pubertal) treated with a placebo; there is a requirement of at least 40 patients per group (× four groups = 160 children total).

The clinical argument for the choice of the principal variable adheres to the fact that the obesity concept is based on the BMI, as the bibliography endorses. However, it should be noted that the BMI in childhood changes substantially with age [30]. Thus, age- and sex-specific cut-off points are needed to define pathology in children via means of a *Z* score [29] to obtain a more accurate value.

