### Statistical analysis

Data will be analyzed using SPSS software version 22 for Windows. Descriptive statistics for all outcomes will be determined. A Kolmogorov-Smirnov test will be used to test data normality. Data that are not normally distributed will be transformed by means of a log10 or square root for analysis. The homogeneity of variances will be determined with a Levene’s test. Normally distributed data will be reported as mean ± standard deviation (SD) and nonparametric data as median (range). The analysis selected to determine the effect of treatment is a linear mixed effects model (LMM), for which the center is considered covariance to adjust the statistical analysis. The fixed effects include time, treatment, adherence, puberty, sex, the interactions *time × treatment*, *time × treatment × puberty* and *time × treatment × sex*. A Bonferroni test will be used to assess the specific differences between the treatments.

Regarding genetic variations, linear regression will be performed to analyze differences in principal variable changes between genotypes and to evaluate independent associated factors.

Moreover, the raw microbiologic data are reported as relative abundances. Differences among times, treatments and puberty are compared using the Mann-Whitney *U* test. Finally, the clustering of the colonic microbiota in both of groups is calculated by a principal component analysis.

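### The mixed model lists no baseline outcome value and no common baseline mean, so the 6-month contrast is less precise than the collected data allow

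*Protocol article*

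**What the plan says.** The first objective concerns the effect of metformin "in reducing BMI in obese children compared with placebo after 6 months" (Objectives). The Sample size section states that "the principal variable is the BMI" *Z* score, and the Abstract also counts changes in biomarkers among the primary outcomes.

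The treatment effect is to be estimated by a linear mixed effects model with adjustment for center. On its terms the Statistical analysis section says: "The fixed effects include time, treatment, adherence, puberty, sex, the interactions", and then names time × treatment, time × treatment × puberty and time × treatment × sex. Between-arm comparisons follow: "A Bonferroni test will be used to assess the specific differences between the treatments".

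Baseline is available for these outcomes. For anthropometry, "The participants attend an initial trial baseline visit, followed by three additional visits at 2-month intervals" (Interventions). For the blood markers, "Three milliliters of blood are collected at the beginning and at the end of the trial" (Blood, urine and fecal sampling). Data from children who withdraw are left out of the analysis (Interim analyses and stopping rules).

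**The concern.** The list contains a free treatment main effect and a time × treatment term. If baseline is a level of time, each arm has its own estimated baseline mean, although randomization makes the two expected means equal. The effect at month 6 is then measured from each arm's own observed baseline, chance imbalance included. That is a change-score analysis. It is valid, but less precise than baseline adjustment whenever ρ is below 1.

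What is at stake is precision that costs nothing to recover. The article argues that earlier pediatric metformin trials were too small. The same model also appears to serve the insulin-resistance, inflammatory and cardiovascular markers, since no other treatment-effect model is named for them. Those markers may correlate less over six months than BMI Z score does.

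**Working it through.** **Plan's own figure.** The article gives no variance or precision figure for the model. Its only related number is 40 children per group. From its inputs ("Its standard deviation is 2.29 in the least favorable case", a difference of 2, α 0.05, power 80%), n = 2 × (1.96 + 0.84)² × 2.29² / 2² ≈ 20.6, so 21 per group, or 27 after dividing by 0.8 for dropout. Splitting α over the six pairwise comparisons of four groups gives 32, and 32/0.8 = 40. The article does not state that step, but it reproduces 40, so I do not call 40 wrong. Nothing below depends on it.

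**Reading the model.** The article does not say outright whether baseline is a level of time.

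- Blood is drawn only at the start and end. For those markers a time effect exists only if baseline is a response. This makes it the natural reading.
- With complete data, categorical time, a treatment effect and time × treatment, the month-6 interaction coefficient equals the difference in raw mean changes. A random-intercept model with these core terms, fitted to simulated data (64 per arm, four visits), gave 0.20035 by both routes.
- If only follow-up visits are modelled, the month-6 contrast is the difference in month-6 means and baseline is not used.
- If time is linear, the contrast is a difference in slopes, again without baseline adjustment.

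**Variance.** Let both time points have variance s² and correlation ρ. Per child:

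- raw change: 2s²(1 − ρ)
- baseline-adjusted: s²(1 − ρ²)
- ratio, adjusted to change: (1 + ρ)/2, so the share saved is (1 − ρ)/2
- compared with unadjusted month-6 values (variance s²), the share saved is ρ²

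The analysed number is 160/2 × 0.8 = 64 per arm. Equivalent size is 64 divided by the ratio. Power is Φ(2.80/√ratio − 1.96), starting from a change contrast with 80% power.

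| Assumed ρ | Change (s² = 1) | Adjusted | Saved vs change | 80% power becomes | 64 per arm worth | Saved vs month-6 means |
|---|---|---|---|---|---|---|
| 0.9 | 0.20 | 0.19 | 5% | 82% | 67 | 81% |
| 0.7 | 0.60 | 0.51 | 15% | 86% | 75 | 49% |
| 0.5 | 1.00 | 0.75 | 25% | 90% | 85 | 25% |

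Simulation with 3,000 runs gave savings against change of 4.0%, 13.1% and 25.6%, in line with the formula. At ρ = 0.95 the saving is 2.5%, and at 0.98 it is 1%.

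**In BMI Z units.** With the article's SD of 2.29 and 64 per arm, the difference detectable with 80% power is 2.80 × 2.29 × √(2v/64), where v is the entry in the second or third column. Adjustment lowers it from 0.507 to 0.494 at ρ = 0.9, and from 1.13 to 0.98 at ρ = 0.5.

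**The case against.** The strongest reply is that this is one paragraph of a journal article. The terms are those that the effects include, and the handling of baseline may be settled in an analysis plan that is not shown. That limits the point but does not remove it. The article does fix a list; adherence, measured after randomization, is on it, and the baseline outcome is not. Every reading of that list considered above leaves baseline unadjusted.

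Second, the loss on the principal variable is small. This stands. If ρ for BMI Z score is 0.9 or more, 80% power becomes 82% at ρ = 0.9 and less above that.

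A reader might infer more than the article supports:

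- *That the result would be biased.* It would not. A difference in changes is a legitimate, unbiased estimator under randomization.
- *That planned power is eroded.* The size was set on the raw SD. The change variance 2s²(1 − ρ) does not exceed s² for any ρ of 0.5 or more, so over the range shown the change contrast is at least as precise as the plan assumed.
- *That 5–25% is a property of this trial.* It follows from assumed values of ρ.
- *That every outcome is affected.* Microbiota abundances are compared by Mann-Whitney tests and genotypes by linear regression.
- *That a joint time × treatment test over four visits costs power.* This depends on time course and covariance. Where the month-6 contrast has 80% power, the 3-df test has about 70% under compound symmetry with a linear build-up, but 83% if the full effect is present by month 2. It cannot apply to markers with two time points, and Bonferroni comparisons between treatments are planned as well. I make no claim on it.

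**Conclusion.** The point holds as one of precision, not validity. As listed, the model makes inefficient use of baseline if baseline is a level of time, and no use of it if only follow-up visits are modelled. On the first reading, adjustment would remove (1 − ρ)/2 of the variance of the 6-month contrast: 5%, 15% or 25% at assumed ρ of 0.9, 0.7 or 0.5. This rests on equal variances at the two time points, complete data and categorical time. For BMI Z score the figure is probably 5% or less; for biomarkers analysed with this model it may be more. Separately, the article does not say which contrast from the model answers the 6-month objective. Both are worth settling before unblinding. Neither threatens the trial's conclusions.

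**What to change.** For outcomes measured at all four visits, model months 2, 4 and 6 as responses with baseline value × time as covariate. Equivalently in aim, keep baseline as a response and constrain the arms to a common baseline mean. For outcomes measured only at start and end, analyse the 6-month value with the baseline value as covariate.

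Name the month-6 metformin minus placebo contrast as the primary test, and say how it is averaged over puberty and sex. If an analysis plan already does this, align the published description with it.

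The cost is a few sentences. Baseline is already collected, the trial status section says recruitment is continuing, and no interim analysis is planned, so the change can be made before the blind is broken. It needs no further children, visits or assays.

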**Discussion:**

This study will assess the differential response of metformin treatment at six months in pre-pubertal and pubertal obese children.

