## Background

The increased prevalence of obesity in pediatric populations is a public health problem [1]. Insulin resistance, impaired glucose tolerance, dyslipidemia, and hypertension are increased in children [2–4]. These metabolic alterations, which primarily result from obesity, begin in childhood and may manifest during adolescence or young adulthood, with diet and a sedentary lifestyle playing decisive roles [5]. In addition to a lifestyle intervention program, pharmacological treatments have been explored. Several drugs have been approved by the Food and Drug Administration (FDA) for the treatment of adult obesity. Currently, orlistat and sibutramine remain widely used in clinical practice in adults. Only orlistat has been approved for use in adolescents [6].

Metformin is an oral anti-hyperglycemic agent approved by the FDA to treat type 2 diabetes (T2D) in adults and children older than 10 years of age. Significant weight loss induced by metformin treatment has been demonstrated in both diabetic and non-diabetic obese adult patients [7]. In contrast, there is insufficient evidence regarding the effects of metformin in pediatric obesity. Several clinical trials have identified modest improvements following metformin treatment in insulin sensitivity in obese children with normal glucose tolerance [8–10], as well as a decrease in the BMI of obese adolescents [11]. In addition, metformin appears to improve lipid profiles in obese children [12, 13]. However, little is known regarding the effects of metformin, along with diet and exercise, on other measures associated with cardiovascular risk and inflammatory biomarkers. Six studies have evaluated the effects of doses of between 1000 and 2000 mg/day for 3–36 months in obese children and/or adolescents on inflammatory biomarkers related to obesity [10, 14–18]. These studies identified promising results, but did not follow a homogeneous distribution according to pubertal stage. Puberty is a very relevant confounding factor with a potential influence on insulin resistance development. Thus, randomized control trials (RCTs) with adequate statistical power appear necessary to enable the examination of these potential confounders [19], apart from a methodology based on a completely homogeneous distribution of factors, such as puberty and sex.

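### The mixed model lists time × treatment × puberty (and × sex) without the two-way terms beneath it, so its F test does not isolate a differential metformin response

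*Protocol article*

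**What the plan says.** The Statistical analysis section chooses the model in these words: "The analysis selected to determine the effect of treatment is a linear mixed effects model (LMM". It then names the terms, beginning "The fixed effects include time, treatment, adherence, puberty, sex, the interactions *time × treatment"; the interactions in full are "the interactions *time × treatment*, *time × treatment × puberty* and *time × treatment × sex". No other section adds an interaction. The software is fixed ("Data will be analyzed using SPSS software version 22 for Windows"), but the coding of the factors is not described.

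The puberty term serves a stated aim. The Discussion paragraph of the Abstract says "This study will assess the differential response of metformin treatment at six months in pre-pubertal and pubertal obese children". The Background adds "Puberty is a very relevant confounding factor with a potential influence on insulin resistance development".

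Anthropometry is measured four times: at baseline, "followed by three additional visits at 2-month intervals". Under Blood, urine and fecal sampling, blood is drawn only at the start and the end, so blood biomarkers have two visits.

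**The concern.** A three-way interaction measures how much a treatment effect over time differs between pubertal stages only if the model also holds the two-way terms beneath it. Without time × puberty, the model has no other place for a change over time that differs between pre-pubertal and pubertal children in both arms alike. Without treatment × puberty, it has no other place for a chance arm imbalance within a stage that is present from baseline.

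The three-way puberty term is the only listed term that addresses the puberty aim. If its F test is read as evidence on that aim, a significant result could arise when metformin acts identically in both stages, or does not act at all. The Background itself expects puberty to influence insulin resistance irrespective of treatment. The sex term is built in the same way and has the same fault.

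**Working it through.** The protocol states no figure for this test, so there is none to reproduce. The check counts degrees of freedom and then works out how often the test rejects when there is no differential effect.

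**Inputs from the protocol article**
- Visits: 4 for anthropometry (Interventions), 2 for blood biomarkers (Blood, urine and fecal sampling).
- Allocation 1:1 within each centre (Randomization).
- 160 children and 20 % loss (Sample size): 160 × 0.8 = 128 completers, or 64 per pubertal stage and 32 per treatment × puberty cell.

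**Assumptions not in the documents**
- Factor coding and equal within-child correlation between visits.
- A stage difference δ in six-month change, in units of the SD of that change. It is the same in both arms and builds up linearly.
- Adherence is left out.

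**Degrees of freedom of the puberty three-way term** (time × treatment × puberty cells minus the parameters of the other listed terms)

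| | 4 visits | 2 visits |
|---|---|---|
| Cells | 4 × 2 × 2 = 16 | 2 × 2 × 2 = 8 |
| Intercept + time + treatment + puberty + time × treatment | 1 + 3 + 1 + 1 + 3 = 9 | 1 + 1 + 1 + 1 + 1 = 5 |
| df of the three-way term as listed | 16 − 9 = 7 | 8 − 5 = 3 |
| of which time × puberty | 3 | 1 |
| of which treatment × puberty | 1 | 1 |
| of which true three-way | 3 | 1 |

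The ranks of the design matrix with the sex terms included agree. At four visits they are 24 with the term and 17 without it, or 21 without it once the two-way terms are in. At two visits they are 12, 9 and 11. The corrected test therefore has 24 − 21 = 3 df or 12 − 11 = 1 df.

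**Noncentrality when there is no differential effect.** With the SD of change set to 1, the within-child error variance is 1/2. The noncentrality is

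λ = (64 × 64 / 128) × Σ(x − x̄)² × δ² / (1/2), where x is time scaled from 0 to 1.

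- Four visits, x = 0, 1/3, 2/3, 1: Σ(x − x̄)² = 5/9, so λ = 32 × (5/9) × 2 × δ² = 35.6 δ².
- Two visits, x = 0, 1: Σ(x − x̄)² = 1/2, so λ = 32 δ².

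**Rejection rate at the 5 % level** (noncentral F on 7 or 3 numerator df, within-child error)

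| δ (SD of change) | λ, 4 visits | Rejects, 4 visits | λ, 2 visits | Rejects, 2 visits |
|---|---|---|---|---|
| 0 | 0 | 5 % | 0 | 5 % |
| 0.1 | 0.36 | 6 % | 0.32 | 7 % |
| 0.2 | 1.42 | 11 % | 1.28 | 13 % |
| 0.3 | 3.20 | 20 % | 2.88 | 26 % |
| 0.5 | 8.89 | 54 % | 8.00 | 64 % |
| 0.8 | 22.76 | 95 % | 20.48 | 97 % |

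Every one of these rejections is false. Once time × puberty is in the model, it takes up the drift, λ for the three-way term is 0 and the rate is 5 % for every δ.

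**Cross-check by simulation** (4000 trials per setting, drift in units of total SD). At within-child correlation 0.8, the SD of change is √(2 × 0.2) = 0.632 total SD, so a drift of 0.3 total SD is 0.3 / 0.632 = 0.47 SD of change. The listed term rejected in 50 % of trials (four visits) and 59 % (two visits), in line with the row for 0.5. With the two-way terms added, rejection was 4–6 % in all settings.

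**Other codings.** If the term is entered as a 0/1 product at two visits, its coefficient takes up 95 % (correlation 0.8) to 97 % (0.9) of the ordinary time × puberty change. Only −1/+1 coding in a balanced design takes up none.

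**The case against.** **The protocol states no rule that this F test decides differential response.** A reader might infer that ordinary pubertal change would be declared a metformin difference. The documents do not go that far: the model is chosen to determine the treatment effect, and specific treatment differences are assessed with Bonferroni comparisons. This stands. With factor coding the listed model is saturated in time × treatment × puberty, so treatment contrasts within each stage, the difference between them and the overall comparison with placebo are not biased. What remains is that the only listed term for the puberty aim does not test it.

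**The list may be incomplete.** The text says that the fixed effects include these terms, and a journal article condenses. But the list spells out one two-way and two three-way interactions, and nothing supplies the others.

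**The drift may be small.** This also stands. BMI Z is already standardised for age and sex, and the Background remark concerns insulin resistance. At 0.1 to 0.2 SD of change the rate is only 6 to 13 %.

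**Two further readings are tempting but unsupported.** One is that the omission costs power. It has no general direction: for a 1 SD effect in one stage only, the listed term rejects in 89–94 % of trials (correlation 0.9 to 0.5) against 70 % for the corrected 3-df test, the excess coming from the absorbed terms. The other is that Table 1, where one centre enrols only pre-pubertal and another only pubertal children, makes time × centre terms necessary. Allocation is 1:1 within each centre, so centre trends common to both arms cancel from the corrected contrast.

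**Conclusion.** The point holds as a fault in the stated model. As listed, the puberty three-way test mixes the differential response with ordinary pubertal change and with treatment × puberty, and the sex term has the same structure. The df count depends only on factor coding and the number of visits. The size of the inflation depends on a drift that the documents do not give: about 5 % with none, 6–13 % at 0.1–0.2 SD of change, 20–26 % at 0.3, and more than half of trials at 0.5. Drift may be small for BMI Z and larger for insulin resistance and other biomarkers. It would be wrong to conclude that the metformin–placebo comparison, or the treatment effect estimated within a stage, is invalid.

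**What to change.** Add time × puberty, treatment × puberty, time × sex and treatment × sex to the fixed effects. State that any claim of differential response by puberty rests on one single-df contrast: the metformin-minus-placebo difference in change from baseline to six months in pubertal children, minus the same difference in pre-pubertal children. Do likewise for sex. Under factor coding this contrast is already unbiased in the listed model; adding the two-way terms also makes the F test valid and protects the result against the choice of coding.

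The cost is a few degrees of freedom and no extra data. Time × centre terms or a repeat in the two centres that recruit both stages are optional and are not needed for validity.

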**Methods/design:**

This is a randomized, prospective, double-blind, placebo-controlled, multicenter trial, which is stratified by puberty and sex. Eighty pre-pubertal (40 boys and 40 girls) and 80 pubertal non-diabetic obese children (40 boys and 40 girls) are being recruited in four Spanish Clinical Hospitals. The inclusion criteria to participate in the RCT include a Body Mass Index (BMI) above the 95th percentile and age 7–14 years. The pubertal stage is determined based on the Tanner criteria. Participants are assigned to two groups in accordance with a randomization schedule and receive 1 g of metformin or placebo for six months in combination with healthy lifestyle recommendations in both groups. The primary outcomes include changes in the BMI Z score and the biomarkers associated with the early appearance of insulin resistance syndrome, inflammation, cardiovascular risk according of the presence of genetic determinants of metformin response, as well as possible modifications in microbiota.

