#### DNA isolation and genotyping

Genomic DNA is extracted from peripheral white blood cells (buffy coat) using the Zymo ZR-96 Quick-gDNA kit (Zymo Research Corporation, Irvine, CA, USA) according to the manufacturer’s instructions. Eleven single nucleotide polymorphisms (SNPs) previously described as being involved in the success of metformin treatment are being selected along several genes: the ataxia telangiectasia mutated (*ATM*, rs11212617); the glucokinase regulatory protein (*GCKR*, rs1260326); the serine-threonine kinase 11 (*STK11*, rs8111699); the peroxisome proliferator-activated receptor gamma, coactivator 1 alpha (*PPARGC1A*, rs2970852); the insulin-induced gene 2 (*INSIG2,* rs7566605); the neuronal growth regulator 1 (*NEGR1*, rs2815752); the solute carrier family 22 (organic cation transporter), member 1 (*SLC22A1*, rs622342); the solute carrier family 47 (multidrug and toxin extrusion), member 1 (*SLC47A1*, rs2289669); the transmembrane protein 18 (*TMEM18,* rs6548238), the potassium channel tetramerization domain containing 15 (*KCTD15*, rs29941); and the fat mass- and obesity-associated protein (*FTO*, rs9939609). Genotyping will be performed in duplicate using TaqMan® OpenArray® Genotyping Plates (ThermoFisher Scientific, Madrid, Spain).

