Additionally, during the last years the importance has been demonstrated of determining the specific contribution of the human gut microbiome to the pathogenesis of obesity to allow for the development of effective treatment strategies. Recently, an elegant study by Forslund et al. published in *Nature* identifies specific disease and drug signatures in the human gut microbiome of T2D patients treated with metformin [21]. By analyzing the dataset without stratifying for treatment regimens, they replicated the majority of previously reported results and showed a large divergence between the study populations. However, composition of gut microbiota from children treated with metformin has not been studied. Taking into account the proven role of the microbiota on childhood obesity development [20], the development of RCTs adjusting the effects according to the human gut microbiome is necessary.

Finally, a considerable amount of pharmacogenetic research has demonstrated that genetic variation is one of the major factors affecting metformin response [35]. Moreover, it has become increasingly clear that the pharmacokinetics of metformin are primarily determined by membrane transporters, including the plasma membrane monoamine transporter, the organic cation transporters (OCTs), the multidrug and toxin extrusion-1 transporter (MATE1), and the critical AMPK. In this RCT, we will analyze the genetic variants previously proved to determine the pharmacokinetics of metformin [36] and a differential response after treatment in obese subjects. Genes included are related to metformin transporters (*SLC22A1* and *SLC47A1*), AMPK and the gluconeogenesis pathway (*ATM*, *STK11* and *PPARGC1A*), insulin sensitivity *(GCKR* and *INSIG2*) and weight loss or weight regain predictors (*FTO*, *TMEM18, NEGR1* and *KTCD15*) Understanding how genetic variation affects metformin response will help to promote more effective use of the drug for the treatment of childhood obesity.

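### The stated genotype regression compares BMI Z change between genotypes and names no genotype-by-treatment term, so as written it does not test the stated objective of differential metformin response

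*Protocol article*

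**What the plan says.** The genetic aim in the Protocol article (Objectives) is effect modification: "metformin differential response will be analyzed according to genetic polymorphisms in drug uptake transporter genes". It is introduced as an addition to the four main objectives. The Discussion repeats the aim of studying variants linked to a different response after treatment.

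The analysis offered for it, in Statistical analysis, is a single sentence: "linear regression will be performed to analyze differences in principal variable changes between genotypes", with a closing clause on evaluating other associated factors. The principal variable is identified under Sample size: "the principal variable is the BMI *Z* score, on which the sample size calculation was based". The sentence does not say whether both arms or only the metformin arm are used, and it mentions neither treatment nor an interaction between genotype and treatment.

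The same section lists the terms of the main mixed model. These include treatment-by-time interactions with puberty and with sex. Genotype is not in that model. The Bonferroni procedure named there concerns differences between treatments.

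The panel, under DNA isolation and genotyping, is "Eleven single nucleotide polymorphisms (SNPs) previously described as being involved in the success of metformin treatment". The Discussion groups these variants by function and calls four of them (FTO, TMEM18, NEGR1 and KCTD15) "weight loss or weight regain predictors".

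**The concern.** Whether genotype changes the response to metformin is a question about a difference of differences: the treatment effect in one genotype against the treatment effect in another. A comparison of BMI Z change between genotypes is a different quantity. It asks whether children with one genotype change more than children with another, for whatever reason.

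Both arms receive lifestyle recommendations, so some change is possible without the drug. A variant that predicts weight change under lifestyle advice alone could then be read as a determinant of metformin response, and a real drug-specific effect could be diluted or missed. For the four variants that the Discussion links to weight loss or regain, that confusion can be foreseen from the document itself.

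**Working it through.** The plan gives no figure for the genetic analysis, so there is none to reproduce. The check asks what each reading of the sentence estimates, and then what the correct test could detect.

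**What each regression estimates.** Let p be the per-allele (or carrier) effect on BMI Z change that is present in both arms, and b the additional effect present only on metformin. The slope is then p on placebo and p + b on metformin. Allocation is 1:1 (Randomization), and genotype is independent of randomised treatment.

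| Regression | Expected genotype coefficient | If b = 0 | If p = 0 |
|---|---|---|---|
| Both arms pooled, genotype only | (p + p + b)/2 = p + b/2 | p | b/2 |
| Metformin arm only | p + b | p | b |
| Both arms, genotype-by-treatment coefficient | (p + b) − p = b | 0 | b |

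Adding treatment as a further covariate to the pooled regression leaves p + b/2 unchanged. Only the interaction isolates b.

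**How this plays out.** Simulation, 3,000 runs, under these assumptions: 128 children, allele frequency 0.3, additive coding, tests at 0.05.

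- Variant with 0.4 SD per allele in both arms (b = 0): significant in 81% of runs when pooled, 53% in metformin only, 4% for the interaction.
- Variant with −0.4 SD per allele on placebo and +0.4 on metformin: 6% pooled, 52% metformin only, 82% interaction.
- No effect at all: 5%, 6% and 5%.

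**Multiplicity.** For 11 independent tests at 0.05 with all nulls true:

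- P(at least one false positive) = 1 − 0.95^11 = 0.431.
- Expected false positives = 11 × 0.05 = 0.55.
- The Bonferroni level is 0.05/11 = 0.0045.

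**Power of the interaction test.** From Sample size: 160 children, 20% loss, SD 2.29, difference of 2 points. Completers are 160 × 0.8 = 128, or 64 per arm. Three assumptions are added: the SD of 2.29 applies to change, genotype is in two categories with shares q and 1 − q, and tests are two-sided.

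SE(interaction) = 2.29 × √[2 × (1/(64q) + 1/(64(1 − q)))]

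- q = 0.5: 2.29 × √0.125 = 0.810
- q = 0.1: 2.29 × √0.347 = 1.349

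This is twice the SE of the pooled genotype main effect. Power for a 2-point interaction is Φ(2/SE − z), with z = 1.96 at 0.05 and 2.84 at 0.05/11.

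- q = 0.5: 2/0.810 = 2.47, giving 70% at 0.05 and 36% at 0.05/11.
- q = 0.3: 62% and 28%.
- q = 0.1: 2/1.349 = 1.48, giving 32% and 9%.

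The interaction detectable with 80% power is 2.27 to 3.78 points at 0.05 and 2.98 to 4.96 points at 0.05/11. By comparison, 2 points is the whole difference on which the trial was sized.

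**The case against.** The strongest reply is that this is one sentence in a condensed article. It gives no covariate list, analysis set or genetic model, and its closing clause about other associated factors leaves room for more terms. A fuller plan may hold an interaction. That stands in part: a reader might infer that the trial has ruled out an interaction test or can never show differential response, and the document does not support that. It does, however, fix the outcome and the contrast, and that contrast is not the one the objective needs. The same section spells out treatment interactions for puberty and sex, so the gap for genotype is more than brevity.

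Other strong readings also fail:

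- *Chance findings are likely.* A 43% probability is below even odds, and it assumes independent tests and all eleven nulls true. The variants are also a pre-specified candidate list. A multiplicity rule for them is something an article may leave to a fuller plan.
- *The effect is halved and the placebo arm is wasted.* Halving applies only if the arms are pooled. An unused placebo arm applies only if they are not. The document states neither, so the two cannot be claimed together.
- *Prognostic effects on placebo are established.* The Discussion makes them plausible for four variants, but the genotyping section describes all eleven in terms of metformin success. They are possible, not documented.
- *The genetic question is a primary outcome.* The Abstract's wording, "The primary outcomes include changes in the BMI Z score and the biomarkers", goes on to mention genetic determinants, while Sample size names BMI Z alone as principal. That is a separate matter of outcome hierarchy and adds nothing here.

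**Conclusion.** The point holds as a mismatch between a stated objective and the stated analysis. Followed as written, the regression estimates p + b/2 (pooled) or p + b (metformin only), and neither separates a variant that modifies the metformin effect from one that predicts weight change in anyone. This result needs only 1:1 allocation and genotype independent of treatment.

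The simulation percentages illustrate the size of the problem under assumed allele frequency and effects; they are not predictions for this trial. The power figures depend on applying 2.29 to change and on the assumed genotype splits, and a smaller SD of change would raise them. Multiplicity across the 11 variants is a secondary matter, to be settled when the model is written down.

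**What to change.** State that the genetic analysis uses both arms. For each variant, regress six-month BMI Z (or its change), adjusted for baseline BMI Z, on treatment, genotype, genotype-by-treatment, puberty, sex and centre. Name the interaction coefficient as the test of differential response. Say which children enter, given that data from withdrawn participants are to be excluded (Interim analyses and stopping rules), and how genotype is coded. Either label the analysis exploratory, with estimates and confidence intervals, or name a procedure that controls the 11 interaction tests.

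The change is to wording only and uses data already being collected. The real cost is precision: on the assumptions above, the test would often miss an interaction as large as the planned treatment difference, and after correction for 11 variants it would miss it more often than not. The plan should therefore also say that a null interaction will not be reported as evidence that response is the same across genotypes.
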